**Substudy #2 (Family Transmission)**									
Other family members (OFM) vital status									X
OFM Morbidity									X
OFM Nasal Swab									X if indicated

#### Household census

A census of all households in the study area was conducted as a part of phase 1 in order to identify all married women age 15–40 years for recruitment, obtain informed consent for participation, and to collect basic information about the household and its structure. Basic information was recorded on age, date of birth, marital status, and pregnancy status for all married women of reproductive age.

#### Pregnancy Identification

Initial identification of pregnant women occurred at the baseline household visit prior to phase 1. Subsequently, all married women between 15 and 40 years of age were visited every 5 weeks and asked about their menstrual period in the preceding 5 weeks. If the woman had her period, the week of the period was recorded and she was visited again 5 weeks later. If she reported no menstrual period, she was offered a urine-based pregnancy test at her home. If the test was positive, she received a pregnancy enrollment interview that included her reproductive history, morbidity in the previous month, date of her last menstrual period, tobacco and alcohol use, and plans for where and by whom she would deliver her baby. We also measured her weight, height, blood pressure, temperature and pulse. Pregnant women were encouraged to attend antenatal care clinics in the public or private sector and to deliver at a certified birthing facility. The study provided education on nutrition, clean delivery, and danger signs at this visit. We also provided her with 90 days of iron-folic acid supplements, a clean birthing kit (included a clean blade, string, plastic tarp, and small plastic disc on which to cut the cord), chlorhexidine ointment for umbilical cord antisepsis, and a single dose of albendazole.

We visited all women monthly throughout their pregnancy to collect pregnancy-related morbidity in the previous month ask about tobacco and alcohol use, and to measure weight, blood pressure, pulse, and temperature.

At the time of pregnancy identification, information on household characteristics was collected and included measures of household socioeconomic status using an asset index, ethnicity, total number of persons in the household, house construction materials and size, source of drinking water, household sanitation practices, type of fuel used for cooking, and whether there were members of the household working outside the local area or country. A complete household roster was also completed at this time including information on age, date of birth, sex, marital status, literacy, educational level, and tobacco use for each member of the household.

#### Trial enrollment visit

Enrollment/vaccination visits occurred at a central location in the VDCs on a rotating basis. Upon arrival at the clinic site, consent to participate was reconfirmed with the woman, her TT history was collected, and a short interview was conducted to reconfirm eligibility. She was listed on the sequential vaccine receipt log and the vaccinator was provided the sealed envelope that matched her serial number. She was subsequently immunized with her assigned treatment in a private location by an unmasked study vaccinator.

#### Pregnancy outcome assessment

When a baby was born, the family contacted a local staff member as soon as possible, often during labor. Project staff then visited the home to collect extensive information on the birth process and the health of the mother and newborn infant(s). Weight, length, head circumference, and temperature of the infant(s) were measured and recorded. One week following delivery, a visit was made to record information on maternal post-partum morbidity.

#### Respiratory morbidity assessment

All women and their newborn infants were visited weekly for morbidity assessment as described previously. Women were visited during pregnancy and through 6 months post-partum. Infants were visited through 6 months of age. Once a woman and her infant reached 180 days post-partum they were discharged from the study.

#### Cause of death assessment

All women and children who died were identified and a verbal autopsy was conducted with members of the family after a culturally appropriate mourning period.

### Laboratory procedures

Mid-nasal specimens were collected using nylon flocked swabs and placed in 1.5 mL of Primestore transport medium, as described. Following local storage at ambient temperature for up to one week, tubes were shipped to the local laboratory, aliquotted into cryovials with secure seals, and stored in a refrigerator prior to shipment at room temperature to the University of Washington Molecular Diagnostics Laboratory, where the samples were stored at −80°C. For PCR analysis, total nucleic acids were extracted from 200 μL of Primestore as described for nasal washes [23] and tested for influenza A and B RNA using real-time reverse transcription (RT)-PCR targeting the influenza A and B matrix genes [24]. Specimens positive for influenza A were subtyped for the seasonal influenza A H1 and H3 subtypes and the novel 2009 H1N1 subtype using real time RT-PCR assays, which employ primers and TaqMan probes that target the specific subtype hemagglutinin genes. Extracted nucleic acid samples were added to a commercial master mix (UltraSense One-Step RT-PCR kit, Invitrogen) containing the forward and reverse primers and the probe in a final volume of 40 μL. RT-PCR cycling conditions are according to the manufacturer’s recommendations for a total of 40 cycles. Positive and negative controls consisting of uninfected human cells and clinical specimens confirmed positive for each influenza A subtype by the Washington State Public Health Laboratory were included in each extraction and PCR run. Samples were considered positive for influenza A or B if the PCR amplification plots crossed the threshold before cycle 40. Each assay had a 95% limit of detection of 10 copies per reaction or 500 copies per swab.

Assays were also conducted for other respiratory pathogens including pertussis and respiratory viruses on a subset of specimens using similar PCR techniques [24,25]. Nasal swabs for culture were collected in UTM Viral Transport Media (Copan Diagnostics, Inc., Murrieta, CA). These tubes were kept in a cooler box after collection and subsequently stored in liquid N_2_ in the field laboratory and transported to Cincinnati where they were stored at −70°C.

Maternal blood was collected using venipuncture into sterile vacutainers. These tubes were kept in a cooler box and transported to the field laboratory. Umbilical cord blood was collected in sterile urine cups by milking the cut umbilical cord. All blood samples were spun, the serum drawn off and then aliquoted prior to storing in liquid N_2_. Serum samples were transported to Cincinnati where they were stored at −70°C.

The serum analysis for antibodies was performed by the Laboratory for Specialized Clinical studies at Cincinnati Children’s Hospital. This lab is certified by the Clinical Laboratory Improvement Amendments (CLIA) and the College of American Pathologists (CAP). Sera were first assessed for antibody to each of the three components of the vaccine by hemagglutination inhibition (HAI) assay using standard methods [26-28]. In brief, sera were treated with Receptor-Destroying Enzyme (RDE; Denka-Seiken, Japan) to remove non-specific inhibitors of hemagglutination prior to testing. Following RDE treatment, the samples were further diluted to 1:10 in Phosphate Buffered Saline (PBS). The sera were then treated with turkey packed red blood cells (RBCs) to remove non-specific agglutinins. The RBCs were spun out of the sera and the samples were ready for testing. Starting at 1:10 dilution, the sera were diluted two-fold through 1:2560 in V-bottom microtiter plates.

Egg-derived, inactivated viral antigens A/California/7/2009 (H1N1)pdm09, A/Perth/16/2009(H3N2 and B/Brisbane/60/2008 (B/Victoria) representative of the vaccine from 2010 to 2012 and A/California/7/2009 (H1N1), A/Victoria/361/2011 (H3N2 and B/Wisconsin/1/2010 (from the B/Yamagata lineage of viruses) representative of the vaccine from 2012 to 2013 were obtained from the Influenza Reagent Resource (www.influenzareagentresource.org). The antigens were added to serially diluted sera, and incubated at room temperature for 30 minutes. RBCs from turkey blood (Viromed Laboratories, Minnetonka, MN) were suspended at a concentration of 0.5% in PBS, added to the serum/viral antigen mixture, and incubated at room temperature for 30 minutes. Plates were tilted and read. The antibody titers were reported as the reciprocal of the last serum dilution to completely inhibit RBC agglutination. Sera without reactivity were assigned a value of < 10. Sera with initial titers of ≥ 2560 were retested at a higher starting dilution in order to obtain a reportable titer. Control sera were established for each antigen and were run in each assay. The assay was valid if the control sera fell within 2 fold of their defined titer. The three antigens used in the assay were shown to be specific by using reference sera supplied by the CDC before use in the HAI. Microneutrilization assays were conducted by the Centers for Disease Control and Prevention according to their standard protocol [29].

### Sample size

Sample size requirements were driven by the primary outcomes for these trials.

All three primary outcomes were considered equivalent in importance and thus, the Type I error was corrected for these multiple primary endpoints. We assumed a total Type I error of 5% across the three primary endpoints, thus needing a sample size corresponding to one-third of this value, or 0.017 for each primary outcome.**Laboratory Confirmed Influenza Illness in Infants 0–6 months of age:** We assumed a baseline rate of 21.6/100 person-years based on the Bangladesh trial [18]. A sample size of 1850 pregnancies (925 in each group) would detect a 50% reduction with 90% power for this endpoint.**Low Birthweight:** Data on the expected incidence of low birthweight came from previous studies we have conducted in this area [30]. The current best estimate is 30.4/100 live births. With 1850 pregnancies, a 25%-30% relative reduction would be detected with 90% power.**Influenza-Like-Illness in Women in Pregnancy and through 6 Months Postpartum:** We assumed a baseline rate of 34/100 person-years based on previous studies in this area [31]. With 1850 pregnancies, a 30% to 35% relative reduction in incidence was detectable with 90% power.

### Data management and analysis

Data were collected on paper forms and checked for errors and missing values before being sent from the field site to Kathmandu for data entry. Data entry screens checked for inconsistencies and out of range values. Errors were corrected by data supervisors based on all relevant forms or sent back to the field for clarification if not time sensitive data.

Two separate analyses will be conducted for each of the annual two cohorts of women vaccinated. A consort diagram will be constructed to show the number of women enrolled, randomized, pregnancy outcomes and live born infants, and losses to follow up through 6 months postpartum. A table will show baseline comparability of the two randomized groups using household and individual maternal level characteristics. The primary outcomes will be compared using relative risk ratios and 95% confidence intervals. Primary outcomes may be stratified by time periods where influenza exposure was high, moderate or low.

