### Outcomes

There were 3 primary and several secondary outcomes for these trials.

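### The sample size controls Type I error at 5% over three primary outcomes (0.017 each), but the analysis text compares them with 95% confidence intervals and carries no correction forward

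*Protocol article*

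**What the plan says.** The Outcomes section of the protocol article sets the number of primary comparisons: "There were 3 primary and several secondary outcomes for these trials".

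The Sample size section commits to a multiplicity correction: "All three primary outcomes were considered equivalent in importance and thus, the Type I error was corrected for these multiple primary endpoints". It gives the total, "We assumed a total Type I error of 5% across the three primary endpoints", and the share of each outcome, "needing a sample size corresponding to one-third of this value, or 0.017 for each primary outcome".

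The Data management and analysis section then describes the primary comparison in one sentence: "The primary outcomes will be compared using relative risk ratios and 95% confidence intervals". It treats the cohorts separately: "Two separate analyses will be conducted for each of the annual two cohorts of women vaccinated". Nowhere does the article give a 0.017 threshold for the analysis, a 98.3% interval, a step-down or hierarchical rule, or a statement that the 95% intervals are descriptive.

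**The concern.** A 95% interval read for whether it excludes a ratio of 1 is a two-sided test at 0.05, three times the level the Sample size section allots to each outcome. The correction governs how many women are enrolled but does not reach the sentence describing the comparison.

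What is at stake is which results count as primary findings. Some observed effects would exclude 1 at 95% but not at 98.3%. The two sections of the article would classify the same result differently, and nothing in the text says which prevails.

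**Working it through.** **Inputs.** From the Sample size section: total alpha 0.05, three outcomes, 0.017 each; 925 per group; low birthweight 30.4%, with a 25% to 30% reduction detectable at 90% power; infant influenza 21.6 per 100 person-years, 50% reduction, 90% power. From Data management and analysis: 95% intervals, cohorts analysed separately. Assumed: two-sided tests (sidedness is not stated), half a year of follow-up per infant for the 180 days, no losses, and the correlations between outcomes, which the article does not give.

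**1. The plan's own alpha.** 0.05/3 = 0.01667, which rounds to the stated 0.017. (3 × 0.017 = 0.051 is only rounding.) The two-sided critical value is 2.394, against 1.960 at 0.05.

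**2. Was the sizing done at the corrected level?** Low birthweight is the cleanest check. With p1 = 0.304 and p2 = 0.75 × 0.304 = 0.228, the difference is 0.076 and the pooled proportion is 0.266.

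- Null standard error: sqrt(2 × 0.266 × 0.734/925) = 0.02055.
- Alternative standard error: sqrt((0.304 × 0.696 + 0.228 × 0.772)/925) = 0.02047.
- At 0.0167: (0.076 − 2.394 × 0.02055)/0.02047 = 1.31, power 90.5%.
- At 0.05: (0.076 − 1.960 × 0.02055)/0.02047 = 1.75, power 96.0%.

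The smallest reduction detectable with 90% power is 24.8% at 0.0167 and 22.0% at 0.05. The lower end of the stated range is therefore reproduced at the corrected level. For infant influenza, 688 to 777 per group would suffice at 0.0167, depending on the formula, so the stated 925 is adequate there too.

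**3. Familywise error per trial if each outcome is read from a 95% interval.**

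- Independent outcomes: 1 − 0.95^3 = 0.143.
- Upper bound under any dependence: 3 × 0.05 = 0.15.
- Three equally correlated normal test statistics (simulated, correlations assumed):

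| Pairwise correlation | Familywise error, 95% intervals |
|---|---|
| 0.1 | 0.142 |
| 0.3 | 0.136 |
| 0.5 | 0.125 |
| 0.8 | 0.099 |

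With 98.3% intervals it is 1 − (1 − 0.0167)^3 = 0.049 if independent, and at most 0.05 under any correlation.

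**4. False claims of benefit only.** Each tail of a 95% interval carries 0.025, so under independence 1 − 0.975^3 = 0.073. At the corrected level each tail carries 0.0167/2 = 0.0083, so 1 − (1 − 0.0083)^3 = 0.025.

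**5. Where the two levels disagree.** On log-ratio intervals with 925 per group:

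- Low birthweight, 281 expected control cases (925 × 0.304): at a 13.5% observed reduction the standard error is 0.074, and 1.960 × 0.074 = 0.145 equals −ln(0.865). At 16.5% it is 0.075, and 2.394 × 0.075 = 0.180 equals −ln(0.835). Observed reductions between about 13.5% and 16.5% exclude 1 at 95% but not at 98.3%.
- Infant influenza, 99.9 expected control events (925 × 0.216 × 0.5): the corresponding zone is about 26% to 31%.

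**The case against.** The best reply is that the analysis sentence states an effect measure and a reporting interval and says nothing about how success is declared. The outcomes are to be compared, which is not the same as judged, with those intervals. A 95% interval for estimation can sit beside a test at 0.017, and the Sample size section, which is never withdrawn, is the only statement on Type I error. The article is condensed, and rules for declaring significance are commonly left to an SAP.

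Part of this stands. The article does not show that the error rate is uncontrolled, and every inflation figure depends on significance being read from the 95% intervals. But no accompanying test at 0.017 is stated. The point is also more than an omission: the article fixes two levels for the same three outcomes and does not reconcile them.

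Two stronger readings are tempting and are not supported:

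- A reader might infer that an ineffective vaccine would be declared effective in about 14% of trials. That figure counts false findings of harm as well as of benefit. The figure for benefit alone is about 7.3%, against about 2.5% at the corrected level.
- A reader might multiply the error over six intervals in the two trials. The plan claims 5% across three endpoints, calls the trials independent and analyses the cohorts separately. A two-trial family is not something it promised to control.

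**Conclusion.** The point holds in conditional form. The article commits to 5% in total and 0.017 per outcome, and its low birthweight figure reproduces at that level, but the correction is not carried into the analysis text. If conclusions are drawn from the 95% intervals, the two-sided familywise error per trial is roughly two to three times the stated 5%: about 14% under independence, never above 15%, and about 10% at an assumed correlation of 0.8. This rests on two-sided tests and on reading the 5% as applying within each trial.

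The design, sample size and data collection are unaffected. What needs settling is the rule by which a primary outcome is called positive.

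**What to change.** In Data management and analysis, state that within each trial conclusions on the three primary outcomes rest either on 98.3% confidence intervals (equivalently, two-sided tests at 0.0167) or on Holm's step-down procedure at a total of 5%, which is never less powerful than Bonferroni. Label any 95% intervals as descriptive. Say explicitly that the 5% applies to each trial separately. If an SAP already contains such a rule, cite it and bring this sentence into line with it.

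The cost is a sentence or two of text. The 98.3% intervals are about 22% wider (2.394/1.960 = 1.22). No power is lost against the plan, since 925 per group was chosen at 0.017. The analysis is written in the future tense, and the Ethical review section has the monitoring board still to review both trials' results, so the rule should be settled before the results are interpreted.

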In addition to the exclusions listed above, women who participated in the first trial were not eligible for the second trial.**Eligibility Phase 1:** Women who were pregnant and between 17 and 34 weeks gestation at the time of trial enrollment for the period April 25, 2011 through April 24, 2012 were eligible for participation in the first trial if they were not excluded based on the above mentioned exclusion criteria.**Eligibility Phase 2:** Women who were pregnant and between 17 and 34 weeks gestation at the time of trial enrollment for the period April 25, 2012 through April 24, 2013 were eligible for participation in the second trial if they did not meet exclusion criteria and if they had not participated in the first trial.

The date of trial enrollment for both phases was defined as the day they presented to the vaccination clinic and were randomized.

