### Primary outcomes

The incidence of laboratory confirmed influenza illness episodes in the infant through 6 months of age.The incidence of low birthweight among newborn infants.Incidence of influenza-like febrile illness (ILI) episodes of the mother during pregnancy and through 6 months postpartum.

Signs and symptoms were ascertained during weekly home visits from the time of maternal enrollment through 180 days following delivery. Every week, field staff visited the home and asked about a series of signs and symptoms for each day in the prior week. For both pregnant and post-partum women, these included fever, persistent cough, sore throat, nasal congestion, myalgia and diarrhea. For infants, these included high fever, cough, difficult or rapid breathing, rhinorrhea, wheeze, dripping ear, diarrhea, difficulty feeding, jaundice and receipt of immunizations. We also ascertained if care was sought for any illness and the type of provider consulted. If a woman or infant had signs/symptoms included in our definitions, a single sterile nasopharyngeal swab with a nylon flocked tip (Copan Diagnostics, Murrieta, CA) was inserted into a nare approximately one-half the distance between the external nostril and the nasal bridge and twisted 360° to obtain a mid-nasal respiratory specimen. It was then placed in Primestore molecular transport medium (Longhorn Vaccines and Diagnostics LLC, Bethesda, MD) and the shaft broken off prior to closing the tube. The test tube was stored at room temperature for up to one week before being transported to the local laboratory. In a subsample of participants, an additional nasal swab was collected from the other nare and placed in viral culture medium.

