#### Definitions

**Laboratory Confirmed Influenza in Infants:** An episode of respiratory illness (with one of more of the following: reported or measured fever (axillary temperature >38°C), cough, wheeze, difficult or rapid breathing, or draining ear plus a positive laboratory test for influenza from nasal swab(s).**Low birthweight (LBW) in newborn infants:** The internationally accepted definition <2500 g was considered to be LBW. Eligible weights were those measured within 72 h of delivery. A secondary analysis included a back calculation to the weight at the time of delivery for all infants based on a statistical model developed from longitudinal weight measures from newborns included in a previous study in this population.**Influenza-Like Illness in Mothers (ILI):** The CDC definition of ILI was used that requires reported or measured fever (axillary temperature >38°C) plus either cough or sore throat on one or more days.

Episodes of influenza-like illness were required to be separated by 7 or more symptom-free days. Laboratory-confirmed influenza for both mothers and infants is not simply a subset of ILI, as ILI required fever as part of the definition and respiratory samples were obtained using a broader definition. This broader clinical definition of signs and symptoms included in the definition for laboratory confirmed influenza reflects the need to identify cases of influenza with a lower severity of clinical signs and symptoms than that included with ILI.

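### One risk-ratio measure is named for all three primary outcomes, although maternal ILI (and, with little consequence, infant influenza) is defined and sized as an episode rate per person-time

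*Protocol article*

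**What the plan says.** - **Outcomes** (Primary outcomes). Two of the three primaries count episodes: "The incidence of laboratory confirmed influenza illness episodes in the infant through 6 months of age" and "Incidence of influenza-like febrile illness (ILI) episodes of the mother during pregnancy and through 6 months postpartum". The third is low birthweight, a yes/no outcome.
- **Repeat episodes** (Definitions). "Episodes of influenza-like illness were required to be separated by 7 or more symptom-free days". Such a rule is chiefly useful if one woman can contribute more than one episode. It is written for ILI, not for laboratory-confirmed influenza.
- **Follow-up.** Eligibility in both phases covers "Women who were pregnant and between 17 and 34 weeks gestation at the time of trial enrollment" (Study population). Illness is ascertained at "weekly home visits from the time of maternal enrollment through 180 days following delivery" (Primary outcomes), and "Once a woman and her infant reached 180 days post-partum they were discharged from the study" (Respiratory morbidity assessment).
- **Sizing** (Sample size). For maternal ILI: "We assumed a baseline rate of 34/100 person-years based on previous studies in this area", with 90% power for a 30% to 35% reduction from 1850 pregnancies. For infants: 21.6 per 100 person-years, a 50% reduction and 90% power. Each primary outcome has a Type I error of 0.017.
- **Analysis** (Data management and analysis). "The primary outcomes will be compared using relative risk ratios", with 95% confidence intervals. That section does not mention rates, person-time or whether repeat episodes count.

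**The concern.** The measure used for sizing is not the measure named for analysis. The Sample size section works in events per person-year for both illness outcomes. The analysis sentence names a ratio of risks, a quantity that needs one yes/no result per person.

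For maternal ILI the gap matters most. A woman enrolled at 17 weeks is watched about half as long again as one enrolled at 34 weeks. The Intervention section adds that in the second trial the enrolment week was itself randomly assigned, so this spread is part of the design. A risk ratio of ever ill to never ill ignores length of observation and drops every episode after a woman's first. At stake are what the primary result means, whether it matches the effect that was powered, and some power.

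**Working it through.** **Inputs from the article.** Maternal control rate 0.34 per person-year; infant control rate 0.216; 925 per arm; alpha 0.05/3 per outcome; entry at 17 to 34 weeks; follow-up to 180 days after delivery.

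**Assumptions.** Two-sided test (z = 2.394). Birth at 40 weeks. Mean maternal follow-up t = 0.78 years, close to the midpoint of the range in step 1. Clustering of episodes within a woman is gamma frailty with variance k = 0, 1 or 2; the article gives no value.

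**1. Maternal person-time.** Entry at 17 weeks: 23 × 7 + 180 = 341 days = 0.93 years. Entry at 34 weeks: 6 × 7 + 180 = 222 days = 0.61 years. Infants: 180 days for all, about 0.5 years, shortened only by death or loss.

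**2. The plan's own ILI figure.** For two Poisson rates, n per arm = (z_α/2 + z_β)²(r1 + r2) / [t(r1 − r2)²], with (2.394 + 1.282)² = 13.51.
- 30% reduction, t = 0.8: 13.51 × 0.578 / (0.8 × 0.102²) = 939.
- 35% reduction, t = 0.6: 13.51 × 0.561 / (0.6 × 0.119²) = 892.

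Both are close to 925, so the stated 30% to 35% range follows from a rate comparison over the plausible follow-up. (The infant figure gives 751 per arm against the planned 925. That is conservative and does not bear on this point.)

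**3. Mothers, ever/never against rate ratio.** At t = 0.78 the mean number of episodes is μ1 = 0.34 × 0.78 = 0.265 in controls and μ2 = 0.7 × 0.265 = 0.186 under a 30% rate reduction.
- Risk of at least one episode, k = 0: 1 − exp(−μ), so 0.233 and 0.169. The ratio is 0.73, a 27% reduction.
- With k > 0: 1 − (1 + kμ)^(−1/k). At k = 1 this gives 0.210 and 0.157, ratio 0.75.
- Rate-ratio power: Φ(|ln RR|/SE − 2.394), SE² = (1/μ1 + 1/μ2 + 2k)/925. At k = 0, SE = 0.0995 and 0.357/0.0995 − 2.394 = 1.19, so 88%. At k = 1, SE = 0.110, so 80%.
- Ever/never power: the usual two-proportion formula with pooled variance under the null.

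| k (assumed) | Rate reduction | Ever/never ratio | Power, ever/never | Power, rate ratio |
|---|---|---|---|---|
| 0 | 30% | 0.73 | 85% | 88% |
| 0 | 32% | 0.71 | 90% | 93% |
| 0 | 35% | 0.68 | 95% | 97% |
| 1 | 30% | 0.75 | 71% | 80% |
| 1 | 35% | 0.70 | 87% | 93% |
| 2 | 30% | 0.76 | 59% | 72% |

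Share of control episodes dropped by ever/never, 1 − risk/μ1: 1 − 0.233/0.265 = 12% at k = 0, and 1 − 0.210/0.265 = 21% at k = 1.

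**4. Infants.** μ1 = 0.216 × 0.5 = 0.108 and μ2 = 0.054. At k = 0 the risks are 0.102 and 0.053, ratio 0.51. Power is 94.7% ever/never and 94.6% for the rate ratio, by the same formulas; the difference is within the approximation. At k = 1 it is 92% against 93%.

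**5. Type I error.** A null simulation (925 per arm, 20,000 runs, maternal follow-up spread over 0.61 to 0.93 years, k = 0, 1, 2, nominal 0.0167) gave 0.015 to 0.017 for ever/never and 0.016 to 0.018 for a person-time rate ratio with robust variance. Both tests are sound.

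**The case against.** The strongest defence has four parts.

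- **The wording is loose.** The article also speaks of an incidence of low birthweight, so its term for the effect measure could cover a rate ratio. This is possible. If so, a short correction settles it, but as printed the sentence allows two different primary analyses.
- **Ever/never is legitimate.** Women are individually randomised within strata of village committee and gestational age, so expected follow-up is balanced between arms and unequal follow-up within arms does not bias the test. This stands. The objection to ever/never is that it answers a different question from the one sized, with some loss of power.
- **The stated power is not refuted.** At 0.78 years without clustering, ever/never still reaches about 90% for a 32% reduction, inside the claimed 30% to 35%, and the rate ratio itself gives only 88% at 30%. This stands too. Only with clustering does ever/never fall below 90% across the whole range (87% at 35% with k = 1).
- **Model and variance details belong in a SAP that is not shown.** Agreed: their absence is no finding. The effect measure, however, is stated here.

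A reader might also infer that the plan yields intervals that are too narrow. In the same simulation, episodes counted and treated as independent yes/no results gave a Type I error of 0.041 for mothers at k = 0 and 0.068 at k = 1, against 0.0167. But the article nowhere says that episodes will be handled that way, and k has no source in it.

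**Conclusion.** The point holds as a mismatch between outcome definition, sizing and named measure, and it is material mainly for maternal ILI. Taken literally as ever/never, the analysis turns a 30% rate reduction into about 27% and costs roughly 3 to 4 points of power with no clustering, or about 9 points at an assumed frailty variance of 1. It drops 12% to 21% of control episodes over the same two cases. These figures rest on birth at 40 weeks, mean follow-up of 0.78 years and a two-sided 0.05/3 test.

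For infants the mismatch is one of wording. Their window is fixed, so the idea that both illness outcomes have unequal person-time by design is not supported, and the loss is negligible (about one point at k = 1).

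The documents do not support a conclusion that the planned test is invalid. It is a plan to correct for clarity and efficiency.

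**What to change.** In Data management and analysis, name the measure outcome by outcome:

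- **Maternal ILI and infant laboratory-confirmed influenza:** incidence rate ratio, all episodes over observed person-time (for example Poisson regression with log person-time as offset), with robust variance clustered on the mother.
- **Low birthweight:** keep the risk ratio.

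If the investigators prefer ever/never for the illness outcomes, the text should say that only the first episode counts and restate power on that basis.

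The cost is wording and standard software, since weekly visits already supply the person-time. If episodes cluster, robust intervals are slightly wider than those from a plain Poisson analysis. The change does not by itself bring power to 90% for a 30% reduction at 0.78 years (88%, or 80% at k = 1). The total of 1850 does not change.
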